#### **Collection and follow-up of adverse events**

Adverse events will be collected as indicated in the CRF. Adverse events likely to be related to the product, whether serious or not, which persist at the end of the trial will be followed up by the investigator until their complete disappearance. The investigator will inform the Medical Responsible or the Monitor of the date of final disappearance of the adverse event and will document it on a correction sheet.

Moreover, any serious adverse event likely to be related to the product and occurring after trial termination should be reported by the investigator to Bio Farma according to the procedure described below.

#### **6.4. Reporting of Serious Adverse Events**

Every serious adverse event occurring throughout the trial should be reported to the Ethic Committee, Regional Vaccine safety Advisory Committee and to the sponsor, by the investigator as **soon as he/she is alerted of it i.e. within 24 hours**, even if the investigator considers that the adverse event is not related to treatment.

Notification should be made:

---

- 
- by phone/email/ by fax; then the investigator should immediately send the **completed alert form** to Ethic Committee, Regional Vaccine Safety Advisory Committee and to the sponsor.

The copy of alert form should be sent to Bio Farma. The investigator should then fill in the **SAE reporting form** as soon as possible, i.e. within five working days or seven calendar days. This form should be signed by the investigator and sent by fax or express mail to the sponsor, Ethics Committee and Regional Vaccine Safety Advisory Committee. Bio Farma as a sponsor should send the reporting form for SAEs-related product (Adverse Drug Reaction) to the NRA within 15 calendar days since the cases was found.

### **6.5 Causality Assessment**

Causality is the relationship between two events (the cause and the effect), where the second event is a consequence of the first. A direct cause is a factor in absence of which the effect would not occur (necessary cause). Sometimes there are multiple factors that may precipitate the effect (event) or may function as co-factors so that the effect (event) occurs).

Causality assessment is the systematic review of data about AEFI case; it aims to determine the likelihood of a casual association between the event and the vaccines(s) received. For individual cases, one tries to apply the evidence available on the basis of the history and time frame of the event to arrive at a casual likelihood.

Case selection of cases for causality assessment should focus on:

- Serious AEFI
  - The occurrence of events above the expected rate or of unusual severity;
  - Signals generated as a result of individual or clustered cases as these could signify a potential for large public health impact.
-

---

WHO Classification:

**I. Case with adequate information for causality conclusion**

A. Consistent casual association to immunization: A case with adequate information for causality conclusion

- A1. Vaccine product-related: An AEFI that is caused or precipitated by a vaccine due to one or more of the inherent properties of the vaccine product
- A2. Vaccine quality defect-related reactions: An AEFI that is caused or precipitated by a vaccine due to one or more quality defects of the vaccine product, including the administration device, as provided by the manufacturer.
- A3. Immunization error-related reaction: An AEFI that is caused by inappropriate vaccine handling, prescribing or administration and that thus, by its nature is preventable.
- A4. Immunization anxiety-related reaction: An AEFI arising from anxiety about the immunization.

B. Indeterminate

- B1. Temporal relationship is consistent but there is insufficient definitive evidence that vaccine caused the event (it may be a new vaccine- linked event). This a potential signal and needs to be considered for further investigation.
- B2. Reviewing factors result in conflicting trends of consistency and inconsistency with casual association to immunization (i.e. it may be vaccine-associated as well as coincidental and it is not possible clearly to favour one or the other.

C. Inconsistent causal association to immunization (coincidental): This could be due to underlying or emerging condition(s) or conditions caused by exposure to something other than vaccine.

---

 WHO. Causality Assessment of an Adverse Event Following Immunization. Geneva: WHO; 2013.

---

---

**Case without adequate information for causality conclusion**

This case is categorized as “unclassifiable” and requires additional information for further review of causality. The available information on unclassifiable cases should be placed in a repository or an electronic database which should be periodically reviewed to see if additional information is available for classification and to perform analyses for identifying signals.

The decision to modify or discontinue the trial, or to break individual or all study codes may be made after mutual agreement between the sponsor and the investigator(s).

**Regulatory Requirements**

In order to comply with current regulations on serious adverse event reporting to Health Authorities and to allow Bio Farma to carry out a precise analysis of the safety of the developed products, the investigator pledges to document accurately the event, to respect notification deadlines, to provide Bio Farma with all necessary information and if requested by the sponsor, to give access to source documents.

Bio Farma pledges to inform Health Authorities as soon as it is informed of any serious adverse event likely to be related to the product. The sponsor also pledges to inform the Authorities of any trial discontinuation and specify the reason for discontinuation.

**Blood sampling**

A blood sample to be taken as soon as possible might be requested in case of serious adverse event if it can help in analyzing the SAE. Four milliliters of blood will be taken in a dry tube.

**Determination of SAE**

Determination of SAE and its causal relationship with the product (vaccine) will be held by Regional Advisory Committee on Adverse Event. This special committee member consists of experts from multidisciplinary field, i.e. medicine (pediatrics, immunology, neurology, vaccine experts, forensic etc.), public health, biostatistics, health law, etc.

---

---

The procedural report of SAE based on the regulation in accordance with Article 21 and 22 Head of National Food and Drugs Agency (Indonesian FDA) Decree No. 21/2015.

---

---

## 7. Evaluation Criteria

### 7.1. Primary Evaluation Criteria

#### 7.1.1. Definition of the Criteria

The main evaluation criteria is defined as the percentage of subjects with an anti-influenza titer  $\geq 1:40$  HI units, 28 days after the last dose immunization.

#### 7.1.2. Parameters to be measured

The anti-influenza antibody serological responses will enable to assess whether the vaccine induce protective antibody levels.

#### 7.1.3. Method and Timing of Measurement

Antibody titers are measured at visit V1 (Day 0), Visit V2 (V1+28(-4/+7) days) for group I-III and at visit V3 (V2+28 days -4 /+7 days) for group IV & V.

The anti-influenza antibody serological responses will be tested by Hemagglutination Inhibition method and will be expressed as HI units.

### 7.2. Secondary Evaluation Criteria

#### 7.2.1. Definition of the Criteria

##### **Immunogenicity**

- a. Serological response to influenza HA vaccine: GMT, percentage of subjects with increasing antibody titer  $\geq 4$  times and or percentage of subjects with transition of seronegative to seropositive 28 days after the last dose of Influenza HA vaccine.
- b. Description of serological response between quadrivalent and trivalent influenza HA vaccine in subjects 9-40 years old.
- c. Description of serological response between each batch number of Quadrivalent Influenza HA vaccine in subjects 9 -40 years old.

##### **Safety**

Safety criteria are defined as the percentage of subjects with local reaction and/or systemic events after vaccination:

- a. Number and percentage of subjects with at least one immediate reaction (local reaction or systemic event) within 30 minutes after each vaccination.
  - b. Number and percentage of subjects with at least one of these adverse events, expected or not, within 72 hours after vaccination.
-

- 
- c. Number and percentage of subjects with at least one of these adverse events, expected or not, between 72 hours to 28 days after vaccination.
  - d. Any serious adverse event occurring from inclusion until 28 days after vaccination.
  - e. Description of adverse events between quadrivalent and trivalent influenza HA vaccine.
  - f. Description of adverse events between each batch number of quadrivalent influenza HA vaccine.

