##### 4.3. Administration

The vaccines will be injected intramuscularly into the left antero lateral thigh region for subjects ≤ 2 years or left deltoid region for subjects > 2 years.

Schedule:

One dose of Quadrivalent or Trivalent Influenza Vaccine at visit 1 (Day 0) for group I, II, III

One dose of Quadrivalent Influenza Vaccine vaccine at at visit 1 (Day 0) and visit 2 (Day 0+28 days-4/+7 days) for group IV & V.

---

---

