### 5.2. Visit Procedures

#### **Sub Study A (Group I-III)**

#### **Visit 1. (D0) 1st blood sample & 1st vaccination**

- Provide subject or parent/guardian(s) with the relevant information concerning the trial.
  - Obtain informed consent/and assent, dated and signed by the subject/parents.
  - Check eligibility criteria.
  - Perform a physical examination.
  - Allocate an inclusion number and randomization code, chronologically to the enrolment of the subject.
  - Take a pre-vaccination blood sample (V1, 4 ml).
  - Inject the 1st dose of the quadrivalent or trivalent influenza vaccine
  - Put the initial name and the inclusion number of the subject on the used vial.
-

- 
- i. Record the code of vaccine in the CRF and the list of participant.
  - j. Keep the subject under observation for 30 minutes and evaluate the immediate local reactions and systemic events.
  - k. Complete CRF.
  - l. Provide a diary card (DC1) to the subject or parent/guardian (s) and inform them how to use and fill the diary card.
  - m. Inform the subject/ parent that they should contact the investigator or the study nurse in case of any Serious Adverse Event.
  - n. Instruct the subject/ parent to return for visit 2.

⇒ **Visit 2 (V1 + 28 (-4/+7) days) 2nd blood**

- a. Perform a physical examination
- b. Check the possible Serious Adverse Events, which occurred since the last visit.
- c. Record the safety data from DC1 to CRF.
- d. Check the concomitant therapies and record in the CRF.
- e. Take a blood sample (V2, 4 ml)
- f. Completion of the study.

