## **6.3. Safety Data Collection and Management Procedures**

The safety data will be collected up to one month after the one injection. During this period, each patient will be provided with a diary card to record the appearance, the duration and the intensity (coded 1,2 or 3) of any local reaction and any systemic event expected or not. The intensity of local reactions will be assessed using a plastic bangle presented in Appendix 4.

For any subject, a local reaction is defined as the occurrence of one or several reaction(s) (expected or unexpected) at the injection site within 28 days following vaccination. Local reactions are:

- ↳ **Local pain**
- ↳ **Redness**
- ↳ **Induration**
- ↳ **Swelling**
- ↳ **Other local reactions**

For any subject, a systemic event is defined as the occurrence of one or several symptom(s) (solicited and unsolicited) within 28 days following vaccination. Systemic events are:

- ↳ **Fever** (axillary temperature  $\geq 38^{\circ}\text{C}$ )
- ↳ **Fatigue**
- ↳ **Muscle pain (Myalgia)**
- ↳ **Other systemic events**

Parents/subjects will measure the intensity of local reactions in using a plastic bangle (See appendix 4). The intensity will be coded in the Diary and CRF as follows:

---

---

|                                                                 | 1=Mild                                      | 2=Moderate                                                  | 3=Severe                                        |
|-----------------------------------------------------------------|----------------------------------------------------|--------------------------------------------------------------------|--------------------------------------------------------|
| Local pain for infants and children (6-35 months)        | Reacts when site is touched                        | Cries when site is touched                                         | Cries when limb is moved                               |
| Local pain for subjects <math>\geq 3</math> years of age | Mild pain to touch                                 | Pain with movements                                                | Significant pain at rest                               |

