#### **7.2.2. Parameters to be measured**

a. GMT, seroprotection and seroconversion rates before and after one dose of immunization will be described per antigen per group vaccine with 95% confidence interval (CI).

b.1 Local reactions and systemic events occurring within 30 minutes after vaccination, 72 hours after vaccination and unexpected event rates, which occurred after 72 hours will be assessed per antigen and per group vaccine with 95% CI.

Any Serious Adverse Events occurring over the study period will be described.

**Subjects** will record the presence of any local or systemic symptom within 28 days following each injection in the diary card. They will answer all questions in the diary for expected and unexpected events during this period.

**The investigator** will report the following data in the CRF:

- The start and end dates of all events.
- The severity (code 1, 2 or 3) of all local reactions.
- Site of local reactions.
- The severity (code 1, 2 or 3) of all systemic events.
- The exact daily maximal axillary temperature up to 3 days after the vaccination.
- The exact maximal axillary temperature of any other fever period.
- The action taken.

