### **Safety analysis**

At each follow-up visit, the following parameters will be computed:

- ◆ Percentage and number of subjects experiencing immediate reactions within 30 minutes of vaccinations.
- ◆ Number and percentage of subjects with at least one local reaction (within 72 hours after each injection), with the frequencies of each type of local reactions (global and broken down according to the size of the reaction when appropriate)
- ◆ Number and percentage of subjects with at least one systemic event (within 72 hours after each injection either related or non related to the vaccine), with the frequencies of each type of event (global and broken down according to the relationship and the severity)
- ◆ Number and percentage of subjects with at least one local reaction (within 72 hours to one month after each injection), with the frequencies of each type of local reactions (global and broken down according to the size of the reaction when appropriate)
- ◆ Number and percentage of subjects with at least one systemic event (within 72 hours to 1 month after each injection either related or non related to the vaccine), with the frequencies of each type of event (global and broken down according to the relationship and the severity)
- ◆ Number and percentage of subjects with at least one Serious Adverse Event, with the frequencies of each type of event (global and broken down according to the relationship and the severity of the event).
- ◆ Description between groups.

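### The closing visit may fall on Day 24–27, so early attenders leave before the 28-day safety period is complete and nothing later is scheduled to observe the missing days

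*Protocol*

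**What the plan says.** **Safety period.** Section 7.2.1 (Safety) lists "Number and percentage of subjects with at least one of these adverse events, expected or not, between 72 hours to 28 days after vaccination" and "Any serious adverse event occurring from inclusion until 28 days after vaccination". In section 7.2.2, subjects "will record the presence of any local or systemic symptom within 28 days following each injection in the diary card", and section 3.6 also sets a 28-day diary. Two places use a different length. Section 6.3 opens with "The safety data will be collected up to one month after the one injection", although the same section defines local and systemic events over 28 days. The safety analysis in section 8.1.3.2 tabulates systemic events "within 72 hours to 1 month after each injection either related or non related to the vaccine".

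**Closing visit.** Section 5.2 and the Schedule & Activities table allow Visit 2 at V1+28 (-4/+7) days. For Groups I–III the steps at that visit include "Record the safety data from DC1 to CRF" and end with "Completion of the study". For Groups IV–V, Visit 2 is also the second vaccination, given at "visit 2 (Day 0+28 days-4/+7 days) for group IV & V" (section 4.3, Administration). The first diary is transcribed there and the second is issued after the injection. Visit 3 closes the study for these groups. It is placed at V2+28 (-4/+7) days in sections 5.2 and 7.1.3, but at Day 0+56 (-4/+7) days in the synopsis and section 3.4.4.

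**Contact outside visits.** Section 3.6 schedules one telephone follow-up, three days after Visit 1. Section 6.3 asks for reports of serious events after trial termination only when they are likely to be related to the product.

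**The concern.** The safety criteria use a fixed 28-day period, but the visit that ends observation may come up to four days before that period is over. The days after an early closing visit are covered by neither a diary nor a scheduled contact. An analysis plan can define denominators, but it cannot recover days that were never observed.

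At stake are the absolute late-event rates and the completeness of the 28-day serious-event criterion. Both serve the secondary objective of assessing safety in all subjects.

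**Working it through.** The protocol states no figure for this point, so there is none to reproduce. The check is date arithmetic on its own windows.

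**Inputs**
- Late safety period (7.2.1): 72 h to 28 days, that is Day 3 to Day 28; 28 − 3 = 25 days.
- Visit 2 window (5.2): 28 − 4 = Day 24 to 28 + 7 = Day 35, 12 permitted days.
- Visit 3 window: V2+28 (-4/+7) in 5.2 and 7.1.3; Day 0+56 (-4/+7) in the synopsis and 3.4.4.
- Subjects (3.1): 540 + 270 = 810.

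**Step 1: days lost at the closing visit.** Days lost = max(0, 28 − d), where d is the day of the visit after the last injection.

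| d | Days observed (d − 3) | Days lost | Share of 25 |
|---|---|---|---|
| 24 | 21 | 4 | 16% |
| 25 | 22 | 3 | 12% |
| 26 | 23 | 2 | 8% |
| 27 | 24 | 1 | 4% |
| 28–35 | 25 | 0 | 0% |

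This applies to Visit 2 in Groups I–III and, under the V2+28 anchor, to Visit 3 in Groups IV–V.

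**Step 2: the other Visit 3 anchor.** Day 0+56 (-4/+7) allows Visit 3 from Day 52 to Day 63. With dose 2 on Day 24 to 35, the interval after dose 2 runs from 52 − 35 = 17 days to 63 − 24 = 39 days. The largest loss is 28 − 17 = 11 of 25 days (44%).

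**Step 3: effect on a rate.** This step assumes a constant hazard over Day 3 to 28; the protocol gives no information on this. The observed rate is 1 − (1 − r)^((d − 3)/25) for a true rate r.
- r = 10%, d = 24: 1 − 0.9^(21/25) = 8.5%. For d = 25, 26 and 27 it is 8.85%, 9.24% and 9.62%.
- r = 10%, visits spread evenly over the 12 days (a second assumption): (8 × 10 + 8.47 + 8.85 + 9.24 + 9.62)/12 = 9.7%.
- r = 5%: 4.2% if all attend on Day 24, 4.8% with even visits.
- r = 20%: 17.1% and 19.4%.

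**Step 4: how many subjects.** The protocol gives no attendance data. With an even spread, 4/12 = 33% of closing visits under the V2+28 anchor would be early (270 of 810). If 10% attended early, the number would be 81.

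**Step 5: one month.** If the wording in 6.3 and 8.1.3.2 means 30 or 31 days, a closing visit exactly on Day 28 is itself 2 or 3 days short.

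**Step 6: dose 2 on Day 24–27 in Groups IV–V.** Here the days up to Day 28 are still observed, because the second diary starts at dose 2. What is open is the dose to which an event in the overlap of 1 to 4 days belongs.

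**The case against.** **The effect is small.** Day 28 is the target, and 8 of the 12 permitted days lose nothing. With even visits, a true 10% becomes 9.7%. In one group of 135 the 95% half-width at 10% is 1.96 × √(0.1 × 0.9/135) = 5.1 percentage points, for a descriptive secondary criterion with no test or margin. Section 6.2 expects mild and transient reactions, so few are likely to appear so late. All of this stands and limits the weight of the point. It does not remove the mismatch between the period defined and the period observed.

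**Randomized comparisons.** A reader might infer that the quadrivalent/trivalent and batch descriptions are biased. The protocol does not support that: Sub Study A is randomized and double blind, with one window for all arms.

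**Double counting in children.** A reader might infer that a reaction after an early dose 2 is counted under both doses. By date alone it could fall in both periods. However, the first diary is transcribed at Visit 2, the second opens after dose 2, and section 7.2.2 requires event dates. Nothing in the protocol says that such an event is counted twice, and an analysis plan can settle the attribution.

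**Serious events.** A reader might infer that the all-cause criterion cannot be met. Section 6.4 requires every serious event during the trial to be reported regardless of relatedness, and subjects are told to contact the investigator about any. The restriction to related events in section 6.3 begins at trial termination, which is not defined there as the subject's last visit; section 3.4.2 puts the end of follow-up in March 2018. Unrelated serious events may be under-collected only if termination means the individual's last visit.

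**Conclusion.** The point holds as a modest gap in data collection. A compliant subject whose last visit falls on Day 24–27 after the last injection has 1 to 4 of the 25 late days unobserved, and no later contact is scheduled. Under the Day 0+56 anchor, the loss after dose 2 can reach 11 days. These day counts follow from the protocol's own windows.

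The size of the bias rests on assumptions: constant hazard, and either even attendance or everyone on Day 24. On those terms a true 10% is seen as 9.7% or 8.5%. The share of early attenders is unknown. What is affected is the absolute late-event rate and, on one reading of trial termination, the collection of unrelated serious events. For dose 2 on Day 24–27 the protocol shows a missing attribution rule, not a demonstrated double count.

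**What to change.** 1. Keep the blood-sampling window. In section 5.2, have subjects whose last visit falls before Day 28 after their last injection continue the diary to Day 28. Add one closing telephone contact on or after Day 28 covering adverse events and all serious events, related or not.
2. Use one length for the safety period throughout: reconcile 28 days (3.6, 7.2.1, 7.2.2) with one month (6.3, 8.1.3.2). If the longer period is meant, move the closing contact to match.
3. Reconcile the two anchors for Visit 3 (synopsis and 3.4.4 against 5.2 and 7.1.3).
4. For Groups IV–V, state in 7.2.1 and 8.1.3.2 that the dose-1 period ends at dose 2 if that comes before Day 28, and that later events count for dose 2 only. Observation continues on the second diary, so this settles attribution without leaving days unobserved.

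**Cost.** One short call per early attender, by a method that section 3.6 already uses, and a few sentences of text. On the two attendance assumptions above, that is 81 to 270 calls. No extra visit, blood sample or subject is needed.
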